#### Evaluation sample

Medical record reviews will be conducted on a random sample of patient who had received care in each practice for at least 1 year at baseline. Reviews will be conducted by research staff separate from the intervention team. The evaluator will be provided with a manual containing detailed instructions and will keep an audit log. A four-part data quality monitoring procedure will be employed consisting of use of a standardized abstraction protocol, extensive training in data abstraction, monitoring of Kappa values between the abstractors, and continuous quality improvement including periodic feedback to abstractors [70].

#### CTH sample

In addition to the evaluation sample described above, data from online CTH assessments, completed by those patients enrolled in CTH, will be used to evaluate the level of implementation of CTH in practices as well as the impact of CTH participation on patient SMS outcomes. The combined samples will result in medical record reviews on up to 1800 patients.

Overall, this study involves no greater than minimal risk to practice member participants or patients. The primary risk is loss of confidentiality. Chart audits are completed on site within the practice and no identifying patient information is removed from the practice. Practice member surveys are anonymous, and we only retain practice (not individual) identifying information. Data are reported only in aggregate. Procedures for minimizing risk are in place and any breeches reported to the governing IRB. Field notes from practice facilitators are monitored regularly by the study team for monitoring trial conduct and possible adverse events.

### RE-AIM evaluation

We will use the RE-AIM framework to guide our evaluation [71–77].

***Reach*** will be assessed by comparing the percentage of eligible T2DM patients for whom there is evidence on chart review that SMS was provided by the practice across the three arms. The reach of the use of CTH will be assessed in two ways in the CTH and CTH + F practices: (1) the percent of eligible T2DM patients with whom CTH is used by the practice (number of eligible T2DM patients enrolled in CTH / total number of eligible T2DM patients with diabetes in the practice), and (2) comparisons of patients who use CTH vs. patients who do not participate in CTH on the basis of key demographic and medical history information.

***Effectiveness*** will be measured in intent-to-treat analyses by several sets of outcome variables collected from the evaluation sample by medical record review. Additionally, evaluation of patient-level “as treated” effects of participation in CTH will be carried out by comparing outcomes for patients enrolled in CTH to those not enrolled on all measures common to CTH.

***Adoption*** will be assessed by the participation and representativeness of practices recruited for the study.

***Implementation*** will be assessed by (a) the extent to which various intervention components are delivered to participants compared to intervention protocol; (b) description of practice-specific modifications to the basic protocol that seem to be effective; and (c) CTH website usage data.

**Maintenance** of the CTH system will be assessed by the extent of continued patient use of the CTH system over the intervention period, as well as the percent of practices at the 18-month follow-up continue using the CTH program.

### Measures

#### Primary Effectiveness Outcomes

Will be obtained from the evaluation sample. HbA1c, LDL, systolic and diastolic blood pressure, and BMI will be abstracted from medical record reviews covering baseline through 18 months post-baseline. For each, the last measure prior to baseline will be used as the baseline measure.

#### Practice SMS: Process of care

The following elements will be assessed in medical record review: presence of a personal care plan with regular updating, evidence of collaborative goal setting, evidence of action planning around prioritized patient goals, evidence of collaborative problem-solving regarding the action planning process, use of community resources to assist in goal attainment, and evidence of ongoing monitoring of progress on identified goals. The chart audit form is available from the authors.

#### Practice Characteristics

Key practice characteristics will be used as covariates and potential moderators in analyses. Practice characteristics will be collected during the practice recruitment process, including level of quality improvement experience, level of PCMH implementation, practice size, setting (rural/urban), level/type of practice organization, baseline performance characteristics related to diabetes, percentage of minority patients in the practice, and percentage of Medicaid or uninsured patients. Additionally, practice members will be surveyed at baseline, 9, and 18 months to assess their perceptions of practice culture and provision of SMS to patients. Providers and staff who participate in surveys receive an information sheet explaining the evaluation purposes and procedures, and completion of the survey provided implied consent. Practice members included for interviews are provided with information by the study team and verbal consent obtained prior to proceeding with the interviews. Waiver of documentation of consent has been approved by the Institutional Review Boards.

#### Secondary effectiveness outcomes from the CTH assessment

Congruent with policy recommendations from the Society of Behavioral Medicine, [78] we use brief scales that are reliable, sensitive to change, and age appropriate in the CTH assessment [79]. These include: diet (intake of saturated fat, fruits and vegetables, salt, and sweetened beverages); [80–82] physical activity (frequency and duration of participation in vigorous, moderate, and walking activity, as well as “screen” time from the International Physical Activity Questionnaire); [83] medication adherence (number of days missed, reasons for missing); [84–86] alcohol intake (number of drinks in past week, number of times imbibed more than limit in past month); [87, 88] tobacco use (whether or not using tobacco, if so, how much;) [89, 90] depression (PHQ-8); [91, 92] and disease-related distress (modified from the Diabetes Distress Scale) [93, 94]. For patients who complete the CTH assessment more than once, we will be able to compare the results over time. For patients who only complete it once over the study period, we will use the data to help describe the sample of patients with whom the practices used CTH.

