### Interventions (see Table 1 and Fig. 1)

#### SMS education (SMS-Ed) arm

The SMS-ED arm serves as an attention control. Project staff will meet onsite with practice clinicians and staff members for two one-hour sessions to discuss what SMS is, why it is important, how primary care plays a role in this process, how others have approached it, and how it can be time and cost efficient for them to engage in SMS as part of standard diabetes care. Practices will have access to a website displaying general and local SMS resources, but will not have access to the formal CTH program. During this session, discussion of the implementation of these resources into the practice will be facilitated. No input will be provided regarding how unique practice characteristics might be utilized for more effective implementation of SMS, and CTH will not be introduced. Practices will be left to utilize these resources and to expand SMS activities as they see fit, without any further study input.

**Table 1 Tab1:** Program Elements across Project Arms

Program Element	SMS-Ed	CTH	CTH + F
Connection to Health computerized intervention program	No	Yes	Yes
Technical assistance with CTH implementation	No	Yes	Yes
Basic instructions on use of CTH	No	Yes	Yes
Assessment of baseline SMS and diabetes care activities	Yes	Yes	Yes
Feedback of assessment and recommendations for practice	No	No	Yes
Generic SMS education	Yes	Yes	Yes
Generic website with SMS resources	Yes	Yes	Yes
Practice facilitation: • Improvement team meetings – 4 over approximately 3 mos. • Workflow revision to implement CTH • Email contacts, other assistance between improvement team meetings and after 3 months as needed • Ongoing feedback of data regarding CTH usage	No	No	Yes

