### Patient samples

#### Patient population perspective

Since allocation of patients occurs at the level of the practice in this trial, all *patients* within a practice will be assigned to the same treatment condition, regardless of the extent to which the individual patient uses the tools provided. Although the intervention can potentially impact the entire population of patients with T2DM, each practice in the CTH and CTH + F arms will selectively utilize CTH with patients, and some patients introduced to CTH in a practice will follow through with it while others will not. Therefore, practices in each of the two arms with CTH will have patients who were and were not exposed to CTH. To preserve intent-to-treat approaches and alleviate potential selection bias at the level of individual patient recruitment, [66–69] we will evaluate the effect of CTH by defining two overlapping patient samples in each practice. The first will be a random sample of all patients with type 2 diabetes mellitus, ages 21 and over diagnosed for a minimum of 12 months, whether or not they participated in CTH – the “Evaluation Sample.” This sample will enable us to examine the effectiveness of the intervention on the primary outcome variables in the intent-to-treat analyses. A second sample in each practice will be comprised of only those patients with diabetes who complete the CTH assessment – the “CTH Sample.” This sample will be used in “as treated” (per protocol) analyses. It should be noted that these two samples are not independent of each other; e.g., many in the CTH sample will be included randomly in the Evaluation Sample. Each sample, however, will be utilized to address different research questions.

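### The secondary effectiveness scales exist only for patients who complete the CTH assessment, so the design gives no controlled estimate of CTH's effect on them

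*Protocol article*

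**What the plan says.** The protocol article gives the patient-reported scales the heading "Secondary effectiveness outcomes from the CTH assessment". On change it says: "For patients who complete the CTH assessment more than once, we will be able to compare the results over time". Patients with a single assessment are to be used only to describe whom the practices reached with CTH.

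The section on the CTH sample names the source as "data from online CTH assessments, completed by those patients enrolled in CTH". It gives these data two purposes: to gauge how far practices implemented CTH, "as well as the impact of CTH participation on patient SMS outcomes". The Methods part of the abstract repeats the second purpose.

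Three statements fix who can have such data:

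- The CTH Sample is "comprised of only those patients with diabetes who complete the CTH assessment" (Patient population perspective).
- In the two arms with CTH, "each practice in the CTH and CTH + F arms will selectively utilize CTH with patients", and only some of the patients introduced to it follow through (same section).
- SMS-Ed practices get a resource website "but will not have access to the formal CTH program". Table 1 enters No for the CTH program in that arm.

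The article also separates its analyses. Patient population perspective assigns the Evaluation Sample to intent-to-treat analyses and the CTH Sample to as-treated ones. The RE-AIM evaluation adds an as-treated comparison of enrolled with non-enrolled patients on the measures they share with CTH.

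**The concern.** An effectiveness outcome needs a comparison: what happened with the intervention against what would have happened without it. These scales are recorded inside the intervention itself, so whoever does not use CTH has no value. Both labels in the article, effectiveness and impact, promise an answer that such data cannot give.

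If the plan is followed as worded, improvement between first and later assessments among returning users could be reported as secondary effectiveness evidence from a cluster-randomised trial. That change would combine any true effect with three others: regression to the mean, secular change in care or behaviour over the study period, and selective return, if patients who are doing well are more likely to complete a second assessment. The data do not separate these.

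**Working it through.** **The plan's own figure.** The only power statement concerns chart review in the Evaluation Sample: 30 patients in each of 12 practices per arm, ICC 1%, a .25 SD difference, two-sided alpha .05.

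- Design effect: 1 + (30 − 1) × 0.01 = 1.29.
- Effective sample per arm: 360 / 1.29 = 279.1.
- Power, normal approximation: Φ(0.25 / √(2/279.1) − 1.96) = Φ(2.95 − 1.96) = 84.0%. With a t test on 22 cluster degrees of freedom it is 80.6%.

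Both agree with the stated figure of more than 80%. It does not carry over to the CTH assessment scales, for which no power is given and to which SMS-Ed contributes no patients.

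**Who has the data.** Setting the sections side by side:

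| Group | CTH assessment scale | Change on the scale |
|---|---|---|
| SMS-Ed patients | none | none |
| CTH and CTH + F, not enrolled | none | none |
| CTH and CTH + F, one assessment | one value, descriptive use | none |
| CTH and CTH + F, two or more assessments | yes | yes |

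No other source is described. Practice SMS: Process of care uses chart review, and the surveys under Practice Characteristics go to practice members, not patients.

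**Which comparisons can be made on these scales.**

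1. CTH versus SMS-Ed, the contrast that the Design section gives for the effect of CTH: not estimable, because one side is empty.
2. Enrolled versus non-enrolled, the as-treated comparison: not estimable, because non-enrolled patients have no assessment. It is possible only for measures abstracted from charts.
3. CTH versus CTH + F among completers: computable, but it addresses facilitation, not CTH. It also conditions on use after randomisation, which facilitation is meant to change.
4. Before versus after in repeat completers: computable, but uncontrolled.

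**Illustration of one bias.** The documents give neither the cut-points in SD units nor the test-retest correlation, so both are assumed here. Take a first and a repeat score that are standard normal with correlation r and no true effect, higher being worse. Among patients whose first score lies above c, the mean first score is φ(c) / (1 − Φ(c)) and the expected repeat score is r times that. The apparent improvement is therefore (1 − r) × φ(c) / (1 − Φ(c)).

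| Cut-point c | φ(c) / (1 − Φ(c)) | r = .5 | r = .6 | r = .7 |
|---|---|---|---|---|
| 0.5 SD | 1.14 | 0.57 | 0.46 | 0.34 |
| 1 SD | 1.53 | 0.76 | 0.61 | 0.46 |

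A second set of assumptions, with repeat users drawn from the worst 50% or worst 30% of first scores and r from .5 to .8, gives 0.16 to 0.58 SD. The result depends heavily on the assumptions.

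**The case against.** The strongest reply is that the authors saw the selection problem and dealt with it. They created the Evaluation Sample to avoid selection at patient recruitment, took all primary effectiveness outcomes from it, assigned the CTH Sample to as-treated use, and said that the two samples answer different questions. The sentence on repeat assessments states only what the data allow, with no test or causal conclusion. This stands, and it narrows the point to the label over these scales and the stated use for impact. It does not remove the point, because the as-treated comparison has no comparator on these scales.

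A reader might go further in three ways, which the documents do not support:

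- That the bias exceeds the trial's .25 SD target. The 0.34 to 0.76 SD range applies to an analysis confined to flagged patients, which is not planned. The Background uses cut-points for patient and clinician reports, and the plan for change covers everyone with more than one assessment. The second set of assumptions goes below .25 SD, and .25 SD is a between-arm difference in chart-review outcomes, not a benchmark for within-person change.
- That a biased CTH versus CTH + F contrast on these scales is planned. No section plans one, so the caution is conditional.
- That the trial cannot show effectiveness. The primary outcomes, their power and their randomised contrasts do not depend on these scales.

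**Conclusion.** The point holds as one of labelling and permitted conclusions. The design gives no randomised or otherwise controlled estimate of CTH's effect on the scales called secondary effectiveness outcomes. What they can provide is a description of CTH users and uncontrolled change in those who returned. This follows from the article's own statements on access and data source, and no choice of analysis method can supply the missing comparator.

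The size of the resulting bias cannot be derived from the documents. The 0.34 to 0.76 SD range is an illustration for flagged patients, resting on assumed cut-points of 0.5 to 1 SD and assumed correlations of .5 to .7. It would probably be smaller in the whole repeat sample.

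**What to change.** - Relabel the CTH assessment scales as descriptive (exploratory) outcomes among CTH users.
- In the section on the CTH sample, and in the matching sentence of the abstract, restrict the wording on impact to chart-abstracted measures, for which the enrolled versus non-enrolled comparison is possible. Keep the use of CTH data for implementation.
- State that effectiveness conclusions, secondary ones included, rest on the Evaluation Sample, as is already laid down for the primary outcomes.
- Show change for all repeat completers, not only flagged patients, with the number of repeaters out of those enrolled.
- If CTH and CTH + F are compared on these scales, mark the contrast as exploratory and conditioned on use after randomisation.

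Current status reports data collection complete and analysis in progress, so collecting the scales in all three arms is no longer open, but relabelling and careful reporting are. The cost is wording. The downside is fewer secondary effectiveness outcomes to report.

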#### Data management

Standardized surveys and chart audit data collection tools and protocols with double data entry for paper forms are used throughout the project. Practice member surveys are administered at initial engagement with practice facilitation. Practice staff and clinicians could complete the survey either via paper copy or through an email link to REDCap. REDCap (Research Electronic Data Capture) is a secure, web-based application designed to support data capture for research studies. (REDCap is supported by supported by NIH/NCRR Colorado CTSI Grant Number UL1 RR025780.) Surveys are anonymous and no individual information was obtained. Data cleaning and coding are supervised by the project statistician. All core study team members will have access to the final dataset.

#### Power and sample size

For the evaluation sample, chart audits of 30 patients per practice will yield 360 patients per arm (1080 total). Assuming an intraclass correlation (ICC) of 1%, this sample size will provide > 80% power to detect a .25 SD difference between any two arms at follow-up or a medium linear trend effect [95, 96]. In a related study the SD for HbA1c was 1.7 and the ICC for patients within practice was < 1%. Thus, a .25 SD difference would translate to a final HbA1c difference of 0.43 between any two arms, adjusted for baseline differences. A similar effect size difference in systolic and diastolic blood pressure, LDL (all ICCs < 1) would translate to a final difference of 4.5 mmHg for systolic BP, 3.0 for diastolic BP, 8.8 for LDL.

#### Quantitative data analysis

For this cluster randomized trial, descriptive statistics will be computed for baseline patient and practice characteristics, initially testing for differences between: (1) different intervention arms and (2) CTH participants vs. non-participants. Patient-level covariates will be screened in bivariate analyses and included in multivariate analysis if they are related to the outcome at *p* < .2, differ between treatment arms, or are associated with dropout. In general, we will employ methods that utilize all available data, assuming ignorable missingness [97–100]. In the event normality assumptions are not met, we will use transformations to normalize distributions, ordinal or Poisson regression where appropriate, and/or the appropriate link function (e.g. logit link for dichotomized measures) [101–103]. We will employ intent to treat analyses using general (generalized) linear mixed models to incorporate data structures that are both hierarchical and longitudinal [66–69, 102, 104]. Hypothesis tests will be two-sided with alpha = .05 or *p* values reported. Goodness of fit statistics and model fitting diagnostics will be used to assess for influential points, outliers, overdispersion and heteroscedasticity and to evaluate alternative model specifications [101]. All statistical analyses will be performed using SAS version 9.2 (SAS Institute Inc., Cary, N.C.).

#### Qualitative data collection and analysis

Extensive qualitative data will be collected across the practices, including observational field notes and in-depth interviews done at baseline and at nine and 18 months from baseline. Field notes will be prepared by the facilitator and/or research staff after each substantive contact with the practice. These data will allow the qualitative analysis team to identify practice issues that impact the adoption, implementation, and maintenance of the SMS activities over time, including CTH in the CTH and CTH + F arms. The facilitator field notes from the improvement team meetings of practices in the CTH + F arm will provide especially rich data for assessing the responses to the facilitation intervention in those practices.

The qualitative analysis will be an iterative process, with the investigators going through cycles of reading, summarizing, and re-reading the data. The interpretative analysis will thus proceed iteratively through five phases of qualitative interpretive analysis described by Miller and Crabtree, [105] resulting in a rich interpretive summary of individual practices and themes running across practices.

#### Dissemination

Final practice assessments will be shared with each practice at the end of the study period. Core study team members will review all manuscripts and abstracts prior to submission. Results will be reported in peer reviewed publications.

#### Current status

Recruitment and data collection are complete as of October, 2017, and data analysis is in progress.

## Discussion

Approximately 70% of patients presenting to primary care practices in the United States have one or more chronic diseases. Primary care clinicians have a difficult time fitting multiple agenda items into brief patient visits and cannot easily meet the SMS needs of their patients with chronic conditions [106]. Approximately half of patients leave their primary care visit without an understanding of what their doctor told them, [106] and only 9% of patients report participating in any shared decision-making regarding their chronic condition [107]. In addition, average adherence rates for lifestyle changes are below 10% [108]. Thus, innovative, time-efficient, and engaging SMS methods need to be developed to assist patients and primary care clinicians and staff. Web-based programs and applications have shown promise for improvement in health behaviors, yet none facilitate patient engagement and shared decision-making between patients and their healthcare team. The use of CTH, with or without practice facilitation to support implementation, should improve SMS for patients with diabetes in primary care practices. This study will provide important information on the implementation of SMS in primary care practices, the effectiveness of an IBCT tool such as Connection to Health, and the use of practice facilitation to assist practices with implementing SMS.

